### Surgery

Depending on the size of the tumor, the size of the breast and patient preferences, the lesion will be removed following the institutions' guidelines for breast cancer management. MR images will be shown to and discussed with the surgeon before the operation. The number and type of surgical procedures (lumpectomy, re-excision, mastectomy, sentinel node biopsy or axillary lymph node dissection) will be reported until 1 year after the LCNB.

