### LCNB

LCNB will be performed under ultrasound guidance or stereotactically. A minimum of four 14 Gauge biopsy specimens per lesion is acquired. The histological diagnosis of the tissue sampled by means of the LCNB provides the definitive diagnosis. Based on histology, patient management will be planned: 'benign lesions' require mammographic follow-up, 'normal breast tissue' requires a repeat LCNB or open breast biopsy and in case of a 'high risk lesion' (i.e. lobular carcinoma in situ, atypical ductal or lobular hyperplasia), 'in-situ carcinoma' or 'invasive carcinoma' require image-guided needle localization followed by surgical excision with appropriate axillary staging (i.e. sentinel node biopsy or axillary lymph node dissection). Patient management will be the same for the MRI and the control group.

If in the intervention group an additional, mammographically occult lesion is detected on the MR images that requires tissue sampling, second-look ultrasound will be performed to determine whether the lesion is ultrasonographically evident and suitable for ultrasound-guided tissue sampling. If the lesion cannot be visualised by means of second-look ultrasound, MRI-guided large core needle biopsy will be performed.

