### Primary outcome

To evaluate whether performing preoperative Breast MRI will improve breast cancer management, we will collect data on all biopsies (including biopsies performed for lesions that were detected on MRI only) and all surgical procedures during 1 year of follow-up after the LCNB. The number of biopsies and surgical procedures in patients in the MRI group will be compared to the number of procedures in the control group.

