## Statistical considerations

### Sample size

The statistical power of the study was calculated for the primary endpoint (reduction in the number of surgical procedures). Based on data of previous studies on nonpalpable suspicious breast lesions and literature, we expect 23% of patients with suspicious nonpalpable breast lesions to require more than one surgical procedure to remove all tumorous tissue [19,22-26]. This number includes patients with mammographically occult multifocal and multicentric disease (8%), patients who require a surgical re-excision because all tumorous tissue could not be removed in one procedure (10%) and patients with a DCIS lesion with a mammographically occult invasive component in the surgical specimen (5%) [19,22-26]. We expect that additional contrast enhanced Breast MRI will reduce this number to 11% due to earlier detection of invasiveness, multifocality and muticentricity and a better 3D depiction of the tumor. With a statistical power of 90% to detect this 12% reduction as significant (p < 0.05, two-sided), we will require 250 women in the control group and 250 women in the MRI group (95% confidence interval 6% to 19%). We consider a reduction larger than 5% clinically relevant.

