### Data-analysis

We will compare the number of all biopsies and surgical procedures within one year after the first LCNB between the MRI group and the control group. To compare the diagnostic performance of MRI (in combination with mammography and ultrasound) and LCNB, a two-by-two table will be constructed in which the results of breast MRI in addition to mammography and ultrasound will be compared to the results of the histology of the tissue sampled at the large core needle biopsy. The positive predictive value will be calculated by dividing the number of correctly identified positives by the total number of positive Breast MRI's. The negative predictive value will be calculated by dividing dividing the number of correctly identified negatives by the total number of negative MRI's. Analyses will be performed for specific subgroups, i.e. microcalcifications and dense breast lesions on mammography. If the positive predictive value of mammography, ultrasound and Breast MRI is sufficiently close the positive predictive value of large core needle biopsy in patients with nonpalpable breast lesions in all patients or in a subgroup of patients, the biopsy in these patients may be replaced by MRI in the future. However, whether MRI can indeed replace LCNB in clinical practice will have to be assessed in a separate study.

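### The primary surgical outcome is a count of procedures, nodal surgery included and with no counting unit, but the trial is powered on the proportion of women needing more than one procedure to clear the tumour

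*Protocol article*

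**What the plan says.** All references are to the protocol article.

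- **Surgery:** "The number and type of surgical procedures (lumpectomy, re-excision, mastectomy, sentinel node biopsy or axillary lymph node dissection) will be reported". The list includes two nodal operations. Reporting runs to one year after the LCNB.
- **Primary outcome:** data are collected on biopsies and on "all surgical procedures during 1 year of follow-up after the LCNB", and then "The number of biopsies and surgical procedures in patients in the MRI group will be compared" with the control group.
- **Data-analysis:** "We will compare the number of all biopsies and surgical procedures within one year after the first LCNB".
- **Sample size:** "we expect 23% of patients with suspicious nonpalpable breast lesions to require more than one surgical procedure to remove all tumorous tissue". This 23% is split into occult multifocal or multicentric disease (8%), re-excision (10%) and DCIS with an occult invasive component (5%). MRI is expected to bring it down to 11%, partly by revealing invasion earlier.
- **LCNB:** high-risk, in-situ and invasive lesions all go to needle localization "followed by surgical excision with appropriate axillary staging (i.e. sentinel node biopsy or axillary lymph node dissection").

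No section says whether two listed procedures performed in the same session count as one or as two.

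**The concern.** Two things do not line up.

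First, the outcome to be compared is a number of procedures, with nodal surgery on the list. The outcome that was powered is a yes/no event per woman, tied to clearing the tumour. These are different endpoints. A result on one does not carry the power computed for the other.

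Second, the counting unit is open, and it matters for one mechanism the trial relies on. If MRI reveals invasion beforehand, a possible benefit is that breast and axillary surgery take place together instead of on two occasions. A count of sessions credits that benefit. A count of listed items does not.

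If the unit stays open, it could be settled after results are known, in a trial where the surgeon sees the MR images.

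**Working it through.** **1. The plan's own figures.** Inputs from Sample size: p1 = 0.23, p2 = 0.11, two-sided 5%, 90% power, 250 per arm.

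- Required n per arm = [1.96·√(2p̄(1−p̄)) + 1.2816·√(p1(1−p1)+p2(1−p2))]² / (p1−p2)². With p̄ = 0.17 this is [1.96·0.5312 + 1.2816·0.5244]² / 0.0144 = 203.8, so 204 (221 with continuity correction). The stated 250 is not reproduced, but it is larger than needed.
- Confidence interval at 250 per arm: 0.12 ± 1.96·√((0.1771+0.0979)/250) = 0.12 ± 0.065, or 5.5% to 18.5%. The article gives 6% to 19%, which agrees apart from rounding.

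Both calculations are for a difference in proportions of women, so the powered endpoint is binary.

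**2. How the unit changes the score.** Suppose a woman has DCIS on biopsy with unsuspected invasion, and suppose her second operation is axillary (an assumption, because the article does not say).

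| Course | Count of listed procedures | Count of sessions |
|---|---|---|
| Lumpectomy, later node biopsy | 2 | 2 |
| Lumpectomy and node biopsy together | 2 | 1 |

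The difference appears only when sessions are counted. The other two components, 8 + 10 = 18 points, concern further breast surgery. Avoiding such an operation lowers the count under either unit.

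**3. Does itemised counting fit 23%?** Preliminary results and Table 2 give 21 non-invasive and 19 invasive carcinomas among 113 LCNB diagnoses: 40/113 = 35.4%. These are diagnoses, not women. The 113 results come from 100 women, so 113 − 100 = 13 results are second or further ones. If every woman has at least one result, the 40 malignant results belong to at least 40 − 13 = 27 women. If each of them had excision plus axillary staging and this counted as two, at least 27% would exceed one procedure before any re-excision, in either arm. That does not fit a control rate of 23%. It depends on staging accompanying the excision of in-situ as well as invasive lesions, as the LCNB section is worded. How often staging is judged appropriate is not given.

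**4. Illustrated effect on power.** Power = Φ{[Δ − 1.96·√(2p̄(1−p̄)/n)] / √[(p1(1−p1)+p2(1−p2))/n]}, with n = 250 and p1 = 0.23 held fixed.

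- No loss: 23% vs 11%, Δ = 0.12. (0.12 − 0.0659)/0.0332 = 1.63, power 94.9%.
- Proportional loss: 12 × 5/23 = 2.6 points, so 23% vs 13.6%, Δ = 0.094. (0.0939 − 0.0678)/0.0343 = 0.76, power 77.7%.
- All 5 points lost: 23% vs 16%, Δ = 0.07. (0.0700 − 0.0695)/0.0353 = 0.02, power 50.6%.

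The article does not divide the 12 points among the mechanisms, so the last two lines are a range under assumption. The third is its extreme: it supposes that MRI would have removed the whole occult-invasion component.

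**The case against.** The strongest reply is that the Surgery section lists types of operation to be recorded and lays down no scoring rule. Elsewhere the article's usage points to repeat operations. Background illustrates several procedures by re-excisions and conversions to mastectomy, and the Discussion speaks of removal in a single attempt. On that reading, lumpectomy with node biopsy is one procedure and the tie disappears. A session convention is also detail that an article may leave to the full protocol.

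Much of this stands. A reader might infer that the article scores each element of a session separately, so that the gain from early detection of invasion cannot appear. The documents do not support that:

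- No section states such a rule.
- The second operation in the 5% component is not identified. If it is a re-excision or a mastectomy, avoiding it registers under any unit. The LCNB section already attaches appropriate axillary staging to in-situ lesions and says management is the same in both groups.
- The power figures apply a binary test and keep a 23% control rate that itemised counting would not produce. They illustrate scale and do not predict the trial's power.

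A reader might also infer that axillary operations pull the comparison toward no effect. If they are equally frequent in both groups, they leave a difference in mean counts unchanged and only add variance.

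One part is not answered. Even on the favourable reading, the sections defining the outcome describe a count of all procedures, and Sample size describes a proportion of women tied to tumour removal. That is a mismatch within the article and not an omitted detail.

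**Conclusion.** The point holds in limited form. The written primary surgical outcome and the powered endpoint differ, and the unit of a surgical procedure is not fixed. Under a literal item count, the benefit at risk is confined to the occult-invasion component, at most 5 of 23 points, and only if its second operation is axillary. The remaining 18 points are not affected.

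The illustrative power range, from about 95% down to 78% or 51%, rests on an unstated split of the 12-point effect and on the control rate staying at 23%. The firmer conclusion is that the 23% and 11% are unlikely to have been derived from an item count that includes nodal staging, so the analysis should not use one as its primary measure. The LCNB and Sample size sections also leave open what second operation the 5% describes, and they need reconciling.

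**What to change.** In Surgery, Primary outcome and Data-analysis, define the primary surgical endpoint as the proportion of women needing more than one operating session within one year of the LCNB, with all procedures in one session counted once. State in Sample size that the 23% and 11% refer to this event.

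Report sentinel node biopsies and axillary dissections by type in a separate table. Do not exclude sessions from the primary comparison according to the judged reason for surgery. Background names node involvement as a cause of repeat surgery, and a reason assigned by a surgeon who has seen the MRI could itself introduce bias.

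Reconcile the LCNB and Sample size sections on which second operation the 5% DCIS-with-invasion component describes.

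The cost is small: revised endpoint wording, and a session date for each procedure. The recording form is not shown, so the date may already be collected. No patient's care changes.

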### Primary outcome

To evaluate whether performing preoperative Breast MRI will improve breast cancer management, we will collect data on all biopsies (including biopsies performed for lesions that were detected on MRI only) and all surgical procedures during 1 year of follow-up after the LCNB. The number of biopsies and surgical procedures in patients in the MRI group will be compared to the number of procedures in the control group.

### Secondary outcome

Previous studies have shown that the positive predictive value of nonpalpable, BI-RADS 5 lesions detected on mammography is 96% [21]. If these lesions are classified as BI-RADS-MRI 5 as well, we expect the positive predictive value to increase further. In the 250 women who will undergo Breast MRI (intervention group), the positive and negative predictive values of Breast MRI in combination with mammography and ultrasound will be determined. If the predictive values are high (in certain subgroups, e.g patients with microcalcifications and dense breast lesions on mammography), LCNB could be omitted in the future in some women. Since all patients in the MONET – study will undergo LCNB, following clinical practice, the number of patients in whom LCNB could possibly be omitted in the future will be estimated based on the calculated predictive values of the MRI.

## Statistical considerations

### Sample size

The statistical power of the study was calculated for the primary endpoint (reduction in the number of surgical procedures). Based on data of previous studies on nonpalpable suspicious breast lesions and literature, we expect 23% of patients with suspicious nonpalpable breast lesions to require more than one surgical procedure to remove all tumorous tissue [19,22-26]. This number includes patients with mammographically occult multifocal and multicentric disease (8%), patients who require a surgical re-excision because all tumorous tissue could not be removed in one procedure (10%) and patients with a DCIS lesion with a mammographically occult invasive component in the surgical specimen (5%) [19,22-26]. We expect that additional contrast enhanced Breast MRI will reduce this number to 11% due to earlier detection of invasiveness, multifocality and muticentricity and a better 3D depiction of the tumor. With a statistical power of 90% to detect this 12% reduction as significant (p < 0.05, two-sided), we will require 250 women in the control group and 250 women in the MRI group (95% confidence interval 6% to 19%). We consider a reduction larger than 5% clinically relevant.

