**Methods/Design:**

The MONET – study (***M***R mammography ***O***f ***N***onpalpable Br***E***ast ***T***umors) is a randomized controlled trial with diagnostic and therapeutic endpoints. We aim to include 500 patients with nonpalpable suspicious breast lesions who are referred for biopsy. With this number of patients, the expected 12% reduction in surgical procedures due to more accurate preoperative staging with Breast MRI can be detected with a high power (90%). The secondary outcome is the positive and negative predictive value of contrast enhanced Breast MRI. If the predictive values are deemed sufficiently close to those for large core biopsy then the latter, invasive, procedure could possibly be avoided in some women. The rationale, study design and the baseline characteristics of the first 100 included patients are described.

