## Background

Breast cancer is the most frequently occurring malignant disease in women with a lifetime risk of 1 in every 8 – 9 women [1]. Like many other Western countries, the Netherlands launched a screening program for breast cancer and since 1998, all women between 50 and 75 years of age are offered biannual mammographic examination. This program reveals approximately 4000 suspicious, nonpalpable breast lesions each year in the Netherlands [2]. In clinical practice, another 3000 nonpalpable lesions are detected annually in women with a high genetic risk or a history of breast cancer [3]. Of all suspicious nonpalpable breast lesions, 10–55% of lesions turn out to be malignant (ductal carcinoma in situ or invasive carcinoma) after large core needle biopsy (LCNB) depending on the aggressiveness of the referral of patients which varies across countries [4]. Subsequently, these patients are scheduled for surgical removal of the malignant breast tumor. In a relatively high proportion of these patients (approximately 20–30%), several surgical procedures (re-excisions or conversions from lumpectomy towards mastectomy) are needed to achieve complete removal of the primary tumor. The reasons for this include unanticipated invasiveness, multifocality, axillary lymph node involvement or incomplete removal of the primary tumor [5]. A more accurate preoperative diagnosis could help to reduce the number of surgical procedures and invasive biopsies.

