## Preliminary results

Between January 2006 and November 2006, 174 patients were eligible for the MONET – study. 108 patients were included in the study (recruitment rate 62%). The reasons for non-participation are listed in Table 1. Eight patients were excluded after randomization (no available histology (n = 5), unanticipated obesity (n = 1), technical failure of MR scanner (n = 1), age over 75 years (n = 1)). Three of the excluded patients were randomized in the control group and 5 in the MRI group. The characteristics of the 100 patients included so far in the MONET – study are summarized in Table 2. The mean age was 56.1 years (range 39.9 – 75.0 years). In these patients, a total of 109 lesions were detected: 108 lesions were detected on mammography and 1 lesion on ultrasound imaging. The majority of the lesions were microcalcifications and classified as BI-RADS 3 or 4. The histological diagnosis of the lesions included 2 non-representative, 9 normal breast tissue, 62 benign lesions, 21 non-invasive carcinomas and 19 invasive carcinomas. So, 35.4% of lesions turned out to be malignant (non-invasive and invasive) after LCNB. Forty-five patients were randomized into the MRI group and 55 into the control group.

**Table 1 T1:** Reasons for non-participation

**Reason non-participation**	**Number of patients (%)**
Unable to lie in prone position	1 (1.5%)
Metal implants	6 (9.0%)
Severe obesity	1 (1.5%)
Claustrophobia	16 (24.0%)
Geographical distance from teaching hospital to MRI too long	18 (27.0%)
Clinical indication for MRI of the breast	1 (1.5%)
Personal reasons	23 (35.0%)
**Total**	**66**

**Table 2 T2:** Characteristics of the first 100 patients included in the MONET – study

n	**100**
Referred from University Medical Center	**30**
Mean age (*range*)	**56.1 **(*39.9 – 75.0*)
Number of lesions detected on mammography	**108**
*density only*	*41*
*microcalcifications only*	*54*
*both*	*9*
*other*	*2*
*unknown*	*2*
BI-RADS classification mammography	
*3*	*45*
*4*	*47*
*5*	*11*
*unknown*	*5*
Number of lesions detected on ultrasound (*mammographically occult lesions*)	**1**
BI-RADS classification ultrasound	
*3*	*1*
*4*	*-*
*5*	*-*
*unknown*	*-*
Diagnosis LCNB	**113***
*non-representative*	*2 (1.7%)*
*normal breast tissue*	*9 (8.0%)*
*benign*	*62 (54.9%)*
*non-invasive carcinoma*	*21 (18.6%)*
*invasive carcinoma*	*19 (16.8%)*

* 4 lesions were sampled twice because of inconclusive results

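### The 23% and 11% reoperation rates fit women with cancer but are applied to all women randomised; on the article's own figures 250 per arm does not give 90% power

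*Protocol article*

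**What the plan says.** All references are to the protocol article.

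- **Sample size.** The control rate is worded for everyone enrolled: "we expect 23% of patients with suspicious nonpalpable breast lesions to require more than one surgical procedure to remove all tumorous tissue". It is the sum of 8% (occult multifocal or multicentric disease), 10% (re-excision for incomplete removal) and 5% (DCIS with an occult invasive component). The MRI rate is 11%. The size follows: "With a statistical power of 90% to detect this 12% reduction as significant (p < 0.05, two-sided"), and "we will require 250 women in the control group and 250 women in the MRI group (95% confidence interval 6% to 19"%). The section adds: "We consider a reduction larger than 5% clinically relevant".
- **Abstract, Methods/Design.** The same power claim is made for 500 patients.
- **Background.** Of suspicious nonpalpable lesions, 10–55% prove malignant, and those patients go to surgery. Then: "In a relatively high proportion of these patients (approximately 20–30%), several surgical procedures" are needed.
- **Study design.** Women are randomised when referred for biopsy, so before the diagnosis is known. In the MRI arm, the scan precedes the large core needle biopsy (LCNB).
- **LCNB.** A benign result leads to mammographic follow-up.
- **Preliminary results.** "So, 35.4% of lesions turned out to be malignant (non-invasive and invasive) after LCNB". Table 2 shows 21 non-invasive and 19 invasive carcinomas among 113 biopsy results in 100 patients.

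**The concern.** The Background and the Sample size section give nearly the same rate for two different groups. In the Background, 20–30% describes patients with a malignant lesion who go to surgery. In the Sample size section, 23% describes all women with a suspicious lesion and is applied to 250 of them per arm. A woman whose lesion is benign cannot contribute to any of the three components. No adjustment for the malignant share is stated.

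This calculation is the only justification given for 500 patients, and the abstract repeats its result. If the rates belong to women with cancer, most randomised women cannot have the event. The difference over all randomised women then shrinks roughly in proportion to the malignant share. A non-significant result from a trial described as having 90% power would be read as evidence that MRI does not reduce reoperation, when the trial may have had little better than an even chance of showing the assumed effect.

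**Working it through.** **Inputs.** Control rate p1 = 0.23, MRI rate p2 = 0.11, n = 250 per arm, two-sided alpha 0.05 (Sample size). Malignant share m = 40/113 = 0.354 (Preliminary results). Since 40 malignant results in 100 women can come from at most 40 women, the share of women with a malignant biopsy is at most 0.40. Range of m: 0.10–0.55; control rate among malignant cases: 0.20–0.30 (Background).

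**Formula.** Two-proportion z-test with d = p1 − p2 and p̄ = (p1 + p2)/2:

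- SE0 = √[2p̄(1 − p̄)/n]
- SE1 = √[p1(1 − p1)/n + p2(1 − p2)/n]
- power = Φ[(d − 1.96·SE0)/SE1]
- expected 95% CI = d ± 1.96·SE1

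**Step 1: the plan's own figures.** For 0.23 vs 0.11 with 250 per arm, SE0 = 0.0336 and SE1 = 0.0332. Power = Φ[(0.12 − 0.0659)/0.0332] = Φ(1.63) = 94.9%. The expected CI is 5.5 to 18.5 points, which agrees with the stated 6 to 19 after rounding. For 90% power, 204 per arm would do (221 with continuity correction). So the stated inputs give about 95%, not 90%; taken alone, that error is on the safe side.

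**Step 2: can 23% be a rate over all women?** If only women with cancer can have the event, the implied rate among them is 0.23/m:

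| Malignant share | Implied rate among women with cancer |
|---|---|
| 35.4% | 65% |
| 40% | 57.5% |
| 55% | 42% |
| 10% | 230% (impossible) |

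The Background gives 20–30%. No share in its range brings the literal reading into line.

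**Step 3: rates placed on women with cancer, m = 0.354.**

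- *All randomised women.* 0.354 × 23% = 8.1% and 0.354 × 11% = 3.9%, a difference of 4.2 points. With 250 per arm, SE0 = 0.0213 and SE1 = 0.0212. Power = Φ[(0.0425 − 0.0417)/0.0212] = Φ(0.04), about 52%. Expected 95% CI: 0.1 to 8.4 points.
- *Women with cancer only.* 250 × 0.354 is about 88 per arm at 23% vs 11%. Power is 56–57% (56.4% at 88, 56.6% at 88.5).

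Exact enumeration of the chi-square test gives 51.9% and 56.6%; Fisher's test gives 45.3% and 49.4%.

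**Step 4: sensitivity.** The relative reduction is held at 11/23; 250 women are randomised per arm.

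| Malignant share | Control rate in cancers | Power, all women | Power, cancers only |
|---|---|---|---|
| 10% | 23% | 18% | 20% |
| 35.4% | 20% | 46% | 50% |
| 35.4% | 23% | 52% | 57% |
| 35.4% | 30% | 64% | 71% |
| 40% | 20% | 51% | 55% |
| 40% | 23% | 57% | 62% |
| 40% | 30% | 69% | 76% |
| 55% | 23% | 72% | 76% |
| 55% | 30% | 84% | 88% |

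The last row takes the most favourable end of both Background ranges and is still below 90%.

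**The case against.** **The denominator is inferred.** The Sample size section literally assigns 23% to all women with suspicious lesions and rests it on cited studies that are not available here. This stands: that the rates belong to women with cancer is not a stated fact. What the article does show is that the Background, the Sample size section and the Preliminary results cannot all be right.

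**No single power value is fixed.** A reader might infer that the true power is about 50%. The documents do not support that precision. The 35.4% counts biopsy results, four lesions having been sampled twice, whereas randomisation is by woman; and the Background allows a control rate other than 23%. A few women whose biopsy was not malignant could also prove to have cancer at excision. The range in Step 4 is the supportable statement.

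**The 5% threshold.** A reader might also infer that the 4.2-point difference falls below the plan's own limit of relevance. That would mix denominators. If 23% and 11% refer to women with cancer, the 5% in the same paragraph may do so too, and 12 points clears it. Nor is the shortfall stable: with a 30% control rate and 35.4% malignant, the difference over all women is 5.5 points.

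**The outcome is a count.** The Primary outcome and Data-analysis sections compare numbers of biopsies and surgical procedures. The power figures here, like the plan's, concern the proportion with more than one surgical procedure. Power for the count comparison cannot be computed from the article. This limits the point, but the plan's 90% rests on the same proportion.

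**Conclusion.** The point holds. The stated 90% power and 6–19% interval cannot be reconciled with the article's own account of who needs repeat surgery and how many lesions are malignant. If the rates apply to women with cancer, power with 250 per arm is about 52% over all randomised women, or about 57% among roughly 88 cancers per arm. Allowing 20–30% control rates and 35–40% malignant, the ranges are 46–69% and 50–76%.

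This rests on three assumptions: only women with cancer can have the event, as the three components imply; the malignant share in the first 100 patients carries over to all 500; and the relative reduction stays at 11/23 when the control rate varies. The first comes from the article's own definitions. Relaxing the second across the Background's 10–55%, with control rates of 20–30%, still leaves power no higher than 84% (all women) or 88% (cancers only).

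**What to change.** 1. In the Sample size section and the abstract, check the cited sources and state which women the 23% and 11% describe. If it is all women with suspicious lesions, explain how that fits the 20–30% in the Background and the 35.4% malignant.
2. If it is women with cancer, replace the 90% and the 6–19% interval. For 500 women: about 52% power over all randomised women, expected difference 4.2 points (95% CI about 0.1 to 8.4), with the range 46–69%; among cancers, about 57%, range 50–76%.
3. State the 5% relevance threshold on the same denominator.
4. Say that the restated power is for the proportion with more than one surgical procedure.
5. Keep all randomised women as the main comparison. Report women with a malignant index lesion as a supporting result only: that group is defined after randomisation and, in the MRI arm, after the scan.

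The cost is rewording and a less favourable stated power; no new data are needed. The correction does not itself restore power. At 35.4% malignant and 23% vs 11% among cancers, 90% power over all women would need about 657 per arm. Recruitment was planned to run to 2008, so the sponsor should say whether it accepts the lower power or enlarges the trial.

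### The stated 90% power does not follow from 23% versus 11% with 250 women per arm, which gives about 94–95%; the gap is conservative only if the 23% applies to every randomised woman

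*Protocol article*

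**What the plan says.** The Sample size section of the protocol article gives a complete set of inputs:

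- Control rate: "we expect 23% of patients with suspicious nonpalpable breast lesions to require more than one surgical procedure".
- MRI-group rate: "We expect that additional contrast enhanced Breast MRI will reduce this number to 11" per cent.
- Power: "With a statistical power of 90% to detect this 12% reduction as significant".
- Test level: "p < 0.05, two-sided".
- Size: "we will require 250 women in the control group and 250 women in the MRI group", presented as what 90% power requires.

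The same sentence prints a 95% confidence interval of 6% to 19% for the reduction. The abstract (Methods/Design) says that with 500 patients the 12% reduction "can be detected with a high power (90" per cent). Neither place mentions a continuity correction, a loss allowance or any other adjustment.

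The 23% is the sum of three parts: disease in several foci or quadrants not seen on mammography (8%), re-excision because tumour was left behind (10%), and DCIS with an unseen invasive component (5%). The Background puts a similar figure on a narrower group. After describing women whose lesions proved malignant and who go on to surgery, it says: "In a relatively high proportion of these patients (approximately 20–30%), several surgical procedures" are needed.

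**The concern.** Two questions arise. First, with both rates, the test level and the size given, the power is fixed to within a point or two by the choice of test, and 90% is not what comes out. A reader who takes 90% at face value has the wrong figure when interpreting a null result.

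Second, the direction of the error is reassuring only if the event rates belong to the women who are randomised. Women enter before biopsy, so many will have benign lesions. If the 23% describes women with cancer, the rate across all randomised women is much lower. The apparent surplus over 90% would then turn into a shortfall.

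**Working it through.** **Inputs (Sample size section).** p1 = 0.23, p2 = 0.11, difference 0.12, mean 0.17, two-sided α = 0.05 (z = 1.960), power 90% (z = 1.282), n = 250 per arm.

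**Size for 90% power (normal approximation, pooled null variance).**
n = [1.960·√(2·0.17·0.83) + 1.282·√(0.23·0.77 + 0.11·0.89)]² / 0.12²
= (1.0412 + 0.6721)² / 0.0144 = 203.8, so **204 per arm**.
With continuity correction: (203.8/4)·[1 + √(1 + 4/(203.8·0.12))]² = 220.2, so **221 per arm**.
The plan's 250 is not reproduced. For 95% power the uncorrected formula gives 251.7, so 252, which is close to 250.

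**Power at 250 per arm.**
- Critical difference: 1.960·√(2·0.17·0.83/250) = 0.0659. Standard error under the alternative: √(0.2750/250) = 0.0332.
- Uncorrected: Φ[(0.12 − 0.0659)/0.0332] = Φ(1.63) = **94.9%**.
- Continuity-corrected (subtract 1/250 = 0.004): Φ(1.51) = **93.5%**.
- Fisher's exact test by enumeration: 94.0%. Unpooled variance: 95.1%. Arcsine: 95.2%.

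No two-sided variant gives 90%. A one-sided test moves further away (166 per arm, or 183 corrected).

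**Which figure is out of line?** At 250 per arm the interval is 0.12 ± 1.96·0.0332 = 5.5% to 18.5%, roughly the printed 6% to 19%. At 204 per arm it would be 4.8% to 19.2%. Rates, size and interval roughly agree with one another; the power does not fit them.

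**Loss that would reconcile 90% with 250.** 1 − 204/250 = 18% uncorrected; 1 − 221/250 = 12% corrected. The only loss reported is 8 of 108 randomised women (7.4%, Preliminary results). Inflating for it gives 204/0.926 = 220 or 221/0.926 = 239, both below 250.

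**If 23% and 11% hold only among women with malignancy.** Multiply both rates by the malignant share m and keep 250 per arm (uncorrected formula). The Preliminary results give 40 malignant diagnoses (21 + 19): 40/113 samplings = 35.4%, 40/109 lesions = 36.7%, and at most 40 of 100 women = 40%. None of these is a reported per-woman share, so using them as m is an assumption. The 10% and 55% are the ends of the Background's range for lesions.

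| m | Control | MRI | Difference (points) | Power |
|---|---|---|---|---|
| 10% | 2.3% | 1.1% | 1.2 | 18% |
| 35.4% | 8.1% | 3.9% | 4.2 | 51% |
| 36.7% | 8.4% | 4.0% | 4.4 | 53% |
| 40% | 9.2% | 4.4% | 4.8 | 57% |
| 55% | 12.7% | 6.1% | 6.6 | 72% |

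For shares of 35–40% the expected difference also falls below the 5% above which the plan calls a reduction clinically relevant.

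**The case against.** The strongest reply is that 90% at 250 is a rounded, prudent statement. A continuity-corrected 221 with a 10% loss gives 221/0.9 = 246, which rounds naturally to 250. At the observed 7.4% loss about 231 women per arm remain, with 91.4% power (corrected) or 93.2% (uncorrected), not far from 90%. A journal article may leave the test and the loss allowance to the full protocol. This stands in part: a reader might infer that 90% and 250 cannot both be right, and the documents do not support that, because an unstated allowance could join them. What remains is that the article presents 250 as the number required by the inputs it prints, and it is not.

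It is also fair that the error is in the safe direction on the stated rates and changes nothing in design or recruitment. That stands too.

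On the denominator, the Sample size section expressly refers its 23% to all women with suspicious lesions and cites different sources from the Background's 20–30%. Under the LCNB section, high-risk lesions also go to excision and normal tissue may lead to open biopsy, so women facing surgery are not only those with malignancy. A reader might therefore go too far in concluding that the true power is about 50%. Whether the 23% is per woman or per cancer cannot be settled from the article. Equally, a reader might take the 95% to mean that the trial is overpowered; that holds only if the 23% is right for every randomised woman.

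**Conclusion.** The 90% in the abstract and the Sample size section does not follow from the printed inputs. They give about 94–95% at 250 per arm (93.5% to 95.2% across methods), and 90% needs 204 to 221 per arm, so 250 is 13% to 23% more than needed (250/221 = 1.13, 250/204 = 1.23). Taken alone this is minor and conservative.

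The protection is conditional on the denominator. The section's wording puts the 23% on all randomised women, while its three components all presuppose cancer and the Background ties a similar figure to women with malignant lesions. The article leaves that tension unresolved. If the rates are per woman with malignancy, power falls to about 51–57% for an assumed share of 35–40%, and lies between 18% and 72% over the 10–55% range; nowhere in that range does it reach 90%. These are conditional figures, resting on the assumption that lesion and sampling counts stand in for the share of women and that women without malignancy contribute no events.

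**What to change.** 1. Keep 250 per arm. In the abstract and the Sample size section, either restate the power as about 94–95% for 23% versus 11%, or name the test and the loss allowance that bring it to 90% (about 12% with continuity correction, 18% without).
2. Say whether the 23% and 11% refer to all randomised women or to those with malignancy, and make the Background and the Sample size section agree.
3. If they refer to women with malignancy, add the resulting power as a sensitivity figure with its assumed malignant share and range, not as a single value.

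The cost is a few sentences in two places and a check of the sources behind the 23%. The rewording needs no extra patients. The conditional figure, if it applies, is less favourable than the one now printed.
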